### Statistical Analysis

Analysis of data extracted from general practice CMR was carried out using the statistical software R. We studied the influence of the anticoagulation regimen by evaluating the cause-specific hazard ratio and the subdistribution hazard ratios of both events. Additionally, we estimated cumulative incidence for both events by direct regression, utilizing the inverse of the probability of censoring weights method [15] with time-varying effects [20]. We will report and interpret both cause-specific and subdistribution analyses. The cause-specific hazard ratio is often interpreted as estimating etiological association, estimating associations between covariates, and the rate at which events occur in those participants who are event-free. The cause‐specific hazard ratio can be interpreted as a rate ratio. Whenever the proportional hazards assumption was violated, we interpreted all hazard ratios as time-averaged effects.

We will determine the (adjusted) incidence and prevalence of AF for each year along with the proportion of incident and prevalent cases treated with nothing, antiplatelet medications only (eg, aspirin), and anticoagulant therapy (warfarin/types of DOACs). We will also determine the number of strokes, transient ischemic attacks, deaths, and bleeds in the incident and prevalent cases per year.

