The aim of this study is to understand the disease and prescribing trends related to AF in general practice. We also aim to develop a system to monitor practice-level indicators for AF of the same trends and evaluate the usability of this system. The primary objective of this study is to investigate if people with newly diagnosed AF treated with DOACs versus warfarin have any difference in stroke or all-cause mortality in long-term follow-up. The secondary objectives of this study are to develop an AF dashboard as an intervention method at a practice level and to evaluate the usability of the AF dashboard.

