#### Exposures and Outcomes

We considered the exposure as continuous anticoagulant prescription for the first time after receiving an AF diagnosis. Although almost all anticoagulant prescriptions in the United Kingdom are issued from primary care if an anticoagulant is started in a hospital, we measured exposure from the first general practice prescription. We excluded patients who had an interval of greater than 90 days between anticoagulant prescriptions.

Outcomes are first records of stroke and all-cause mortality based on previously published Read codes [16,17] Stroke was included regardless of etiology, an approach used in other studies [18,19]. Study participants were followed for stroke and all-cause mortality till the end of the study period.

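### All-cause mortality is compared between DOAC and warfarin only through two-event competing-risk measures, which as written describe death without prior stroke

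*Protocol article*

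**What the plan says.** The Introduction of the protocol article sets as primary objective whether people with newly diagnosed AF on DOACs or warfarin "have any difference in stroke or all-cause mortality in long-term follow-up". Under Exposures and Outcomes, "Outcomes are first records of stroke and all-cause mortality", and "Study participants were followed for stroke and all-cause mortality till the end of the study period".

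The Statistical Analysis section then studies the effect of the anticoagulant regimen by "evaluating the cause-specific hazard ratio and the subdistribution hazard ratios of both events". It adds that "we estimated cumulative incidence for both events by direct regression, utilizing the inverse of the probability of censoring weights method", with time-varying effects. It promises to report and interpret both the cause-specific and the subdistribution results, and describes the cause-specific ratio in terms of "the rate at which events occur in those participants who are event-free".

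The only other use of deaths is a yearly tabulation of the "number of strokes, transient ischemic attacks, deaths, and bleeds in the incident and prevalent cases per year". That is a count over time, not a comparison of the two drugs.

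**The concern.** The two events are stroke and death from any cause, and their relation is one-sided. Death prevents a later stroke, so it competes with stroke. Stroke does not prevent death, so death from any cause has no competing event.

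If both events go into one competing-risk model, a patient leaves the at-risk state at the first event. Someone who has a stroke and dies a year later counts as a stroke and never as a death. The death outcome is then death without a prior recorded stroke, which is not the outcome named in the objective.

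Two things are at stake. The article's text on anticoagulation says its aim is to lower thromboembolic risk, so deaths that follow a stroke are one direct way in which a difference between drugs could reach mortality, and this analysis leaves them out. In addition, the group with fewer strokes keeps more people at risk of dying stroke-free. That raises its cumulative incidence of stroke-free death even if its overall mortality is lower.

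**Working it through.** **What follows from the text.** The subdistribution hazard for an event keeps in the risk set those who have already had a competing event. Without a competing event it equals the ordinary hazard. The only other event named is stroke. So a separate subdistribution ratio for death implies that stroke is coded as competing with death. No ordinary all-cause comparison of DOAC with warfarin is described.

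**Size.** The article gives no event rates, sample size or power for phase 1, so there is no figure to reproduce and every rate below is an assumption. Model: constant hazards, three states (event-free, after stroke, dead). Everyone starts stroke-free, in line with the exclusion of previous stroke under Case Ascertainment.

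- Stroke rate s: 0.02 per year on warfarin; 0.02 × 0.70 = 0.014 on DOAC
- Stroke-free death rate d: 0.05 per year in both groups
- Death rate after stroke p: 0.25 per year
- Time T: 5 years

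Formulas, with L = s + d:

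- Stroke first: (s/L)(1 − e^(−LT))
- Death first: (d/L)(1 − e^(−LT))
- Alive after stroke at T: s(e^(−LT) − e^(−pT))/(p − L)
- Death after stroke: stroke first minus alive after stroke

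Warfarin, L = 0.07, e^(−0.35) = 0.7047:

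- Stroke first: (0.02/0.07) × 0.2953 = 0.0844
- Death first: (0.05/0.07) × 0.2953 = 0.2109
- Alive after stroke: 0.02 × (0.7047 − 0.2865)/0.18 = 0.0465
- Death after stroke: 0.0844 − 0.0465 = 0.0379
- All deaths: 0.2109 + 0.0379 = 0.2488

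DOAC, L = 0.064, e^(−0.32) = 0.7261:

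- Stroke first: 0.0599
- Death first: 0.2139
- Death after stroke: 0.0268
- All deaths: 0.2139 + 0.0268 = 0.2407

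Comparison:

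- All-cause risk ratio: 0.2407/0.2488 = 0.967
- Death-first risk ratio: 0.2139/0.2109 = 1.014
- Cause-specific hazard ratio for stroke-free death: 0.05/0.05 = 1.00
- Share of deaths not counted on warfarin: 0.0379/0.2488 = 15%
- Share of deaths not counted on DOAC: 0.0268/0.2407 = 11%

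**Sensitivity to the equal-mortality assumption.** Stroke-free mortality on DOAC is lowered and all else kept:

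| Stroke-free death rate on DOAC | Death first | Death-first ratio | All-cause ratio |
|---|---|---|---|
| 0.050 | 0.2139 | 1.014 | 0.967 |
| 0.049 (2% lower) | 0.2102 | 0.997 (0.2102/0.2109) | 0.952 |
| 0.045 (10% lower) | 0.1948 | 0.92 | 0.89 |

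**Range.** With d = 0.05 in both groups, p = 0.25, warfarin stroke rates of 0.01 to 0.04 per year, stroke hazard ratios of 0.5 to 0.8, and 5 or 10 years, ratios of log(1 − risk) run from 1.005 to 1.11 for stroke-free death and from 0.99 to 0.85 for all-cause death. Between 8% and 36% of warfarin deaths follow a stroke.

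**Simulation** (100,000 per group, warfarin stroke rate 0.02, stroke hazard ratio 0.5, 10 years):

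| | Cause-specific, stroke-free death | Subdistribution, stroke-free death | All-cause |
|---|---|---|---|
| No frailty | 0.99 (true value 1) | 1.04 | 0.91 |
| Shared frailty, log-SD 1.0 | 1.03 | 1.09 | 0.93 |

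**The case against.** A reader might infer that the plan discards every death after a stroke. The article does not say so. It never uses the word competing and gives no rule for censoring at stroke, and its statement that follow-up for mortality runs to the end of the study suggests that such deaths are recorded. The sentence about event-free participants is a general remark on interpretation, and event-free may mean free of the event being analysed. A cause-specific Cox model for death that is not censored at stroke is an ordinary all-cause Cox model, and the text does not exclude that. This stands, so for the cause-specific result the point is conditional. It does not rescue the subdistribution result: either stroke competes with death and the outcome is stroke-free death, or nothing competes and a separate subdistribution ratio for death has no meaning. The text needs correcting in both cases.

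A reader might also infer that the analysis will make DOACs look harmful. That is too strong. The cause-specific ratio is 1.00 in the illustration, and the article commits to reporting it beside the subdistribution ratio. The reversal rests on near-equal stroke-free mortality, whereas the Introduction describes DOAC mortality as similar to or better than that on warfarin. The gap in the base case is also only about 5% in relative terms, on assumed rates.

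Nor do the documents show that stroke deaths are the main way in which anticoagulants affect mortality. In the illustration about 85% of warfarin deaths do not follow a stroke, and bleeding, which the article counts, is another possible route.

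A condensed article may leave event coding to a fuller plan. The objection here is to the effect measures that the article states for both events, which do not match the outcome it names.

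**Conclusion.** The point holds as a mismatch between the named outcome and the stated analysis. The subdistribution and cumulative incidence results for death, as written, describe death without prior stroke. The cause-specific result does too if follow-up is censored at stroke. No all-cause comparison of DOAC with warfarin is stated, although the objective asks for one.

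The mismatch rests on the text alone. Its numerical size rests on assumed constant hazards. Under near-equal stroke-free mortality, the group with fewer strokes can show a death ratio slightly above 1 on the subdistribution or cumulative incidence scale while its all-cause mortality is lower. The effect is small when strokes are rare. Where the sign does not reverse, the outcome is still not the one named.

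**What to change.** Reconcile Exposures and Outcomes with Statistical Analysis:

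- Analyse all-cause mortality as time to death from any cause, using an ordinary Cox model and Kaplan-Meier or adjusted survival curves, with follow-up continuing through stroke.
- Keep the cause-specific, subdistribution and cumulative incidence analyses for stroke, with death as its competing event.
- If a two-event result for death is still shown, label it *death without prior stroke* and do not present it as all-cause mortality.

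The cost is a few sentences and one standard model. Follow-up for mortality to the end of the study indicates that the data are in hand. The Results section says the analysis is complete and the papers are under review, so the change is an added model and a corrected label in the reports.

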**Methods:**

The study was conducted in 2 phases. The initial phase was a quantitative analysis of routinely collected primary care data from the Oxford Royal College of General Practitioners Research and Surveillance Center (RCGP RSC) sentinel network database. AF cases from 2009 to 2019 were identified. The study investigated the impact of the use of anticoagulants on complications of AF over this time period. We used this dataset to examine how AF was managed in primary care during the last decade. The second phase involved development of an online dashboard for monitoring management of AF in general practice. We conducted a usability evaluation for the dashboard to identify usability issues and performed enhancements to improve usability.

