## Methods

### Study Design

This study combines qualitative and quantitative methods and therefore, was planned as a mixed method study [9-11]. It was run within the Oxford Royal College of General Practitioners Research and Surveillance Centre (RCGP RSC) sentinel network of general practices. The mixed method study was conducted in 2 phases. Phase 1 was a quantitative analysis of AF data. We conducted a repeated cross-sectional study to identify those patients diagnosed with AF during 2009-2019 and identified current therapeutic management of their AF. Phase 2 involved development and evaluation of a dashboard for monitoring data quality for AF. The dashboard provides the general practices in the RCGP RSC sentinel network an access to quality indicators related to AF management that are updated weekly.

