## Results

We received funding for both phases in January 2019 and received approval from RCGP RSC research committee in March 2019. We completed data extraction for phase 1 in May 2019 and completed analysis in December 2019. We completed building the AF dashboard in May 2019. We started recruiting participants for phase 1 in May 2019 and concluded data collection in July 2019. We completed data analysis for phase 2 to in October 2019. As of October 2020, the publications reporting the results are under review.

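### Yearly complications are planned as raw counts over 2009-2019 although extraction finished in May 2019: on calendar years the 2019 counts cover at most about 41% of a year, and earlier counts move with the number of AF cases

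*Protocol article*

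**What the plan says.** The protocol article sets the phase 1 window in two places. The abstract's Methods paragraph says "AF cases from 2009 to 2019 were identified", and Study Design says "We conducted a repeated cross-sectional study to identify those patients diagnosed with AF during 2009-2019". The Results section dates the data: "We completed data extraction for phase 1 in May 2019 and completed analysis in December 2019". Exposures and Outcomes gives the end of follow-up without a calendar date: "Study participants were followed for stroke and all-cause mortality till the end of the study period".

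The second paragraph of Statistical Analysis sets out the yearly outputs. AF itself is described by adjusted measures: "We will determine the (adjusted) incidence and prevalence of AF for each year". Treatment is described as a proportion of incident and of prevalent cases. Complications are different: "We will also determine the number of strokes, transient ischemic attacks, deaths, and bleeds in the incident and prevalent cases per year". No rate, person-time or adjustment is attached to these events.

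**The concern.** Two features of the yearly event series could mislead.

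- **Part-year 2019.** The period runs to 2019, but the data cannot reach past May of that year. A count for 2019 set beside counts for full years would look like a sharp fall in strokes, TIAs, deaths and bleeds at the end of the period in which DOACs were taken up.
- **Counts as the measure.** The Introduction and the Discussion both describe AF incidence as rising. A count is risk multiplied by the number of people at risk and the time they are observed. If the number of AF cases grows, the count grows at unchanged risk, and it can rise while the risk falls.

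This matters because the abstract's Objective includes evaluating how DOAC use bears on AF complications. Exposures and Outcomes limits the modelled outcomes to stroke and all-cause mortality. For TIAs and bleeds, the yearly number is therefore the only analysis the article states, and bleeding is the harm that the Introduction weighs against anticoagulation.

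**Working it through.** The article gives no event count, rate or sample size for phase 1, so there is no figure of its own to reproduce. The check is direct arithmetic.

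**Inputs from the document**

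- Period: 2009-2019 (abstract, Study Design).
- Extraction completed: May 2019 (Results). The latest possible data date is therefore 31 May 2019.
- Event measure: number per year (Statistical Analysis).

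**Assumptions, not in the document**

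- Year means calendar year, and 2019 is shown.
- Events are spread evenly over the year.
- Yearly growth in the number of AF cases is 2% to 8%, as a range.
- Any yearly change in risk is as stated below.

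**Step 1: share of 2019 observed.** Share = days from 1 January to the data cut / 365. Apparent fall at constant risk and constant number of cases = 1 − share.

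| Data cut | Share of 2019 | Apparent fall |
|---|---|---|
| 31 May | 151/365 = 41% | 59% |
| 30 April | 120/365 = 33% | 67% |
| 31 March | 90/365 = 25% | 75% |

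**Step 2: could growth hide the fall?** The ratio of the 2019 count to the 2018 count is (1 + g) × 151/365, where g is yearly growth in cases. At g = 2% it is 0.42, and at g = 8% it is 0.45. For the 2019 count to equal that of 2018, the number of cases would have to grow by a factor of 365/151 = 2.4 in one year.

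**Step 3: counts over the complete years.** From 2009 to 2018 there are nine yearly steps. At constant risk the count ratio is (1 + g)^9, while the ratio of rates per person-year is 1.0.

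| Assumed growth per year | Count 2018 / count 2009 |
|---|---|
| 2% | 1.20 |
| 3% | 1.30 |
| 5% | 1.55 |
| 8% | 2.00 |

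**Step 4: can the direction be wrong?** With 5% yearly growth and risk falling 3% a year, the count ratio is (1.05 × 0.97)^9 = 1.18 and the rate ratio is 0.97^9 = 0.76. Counts rise by 18% while the rate falls by 24%.

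**Step 5: what person-time does.** If 2019 events are divided by person-time up to the cut, the 151/365 appears in both numerator and denominator and cancels. At constant risk the 2019/2018 rate ratio is then 1.0, whatever the cut date or the growth.

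**The case against.** The strongest reply is that the final-year fall is inferred. The article does not define a year or a data cut, and does not say that 2019 appears as a full-year point. Twelve-month periods ending by spring 2019 would fit the stated window and contain complete years. This stands, and it makes the 2019 part of the point conditional.

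A second reply is that cut dates, part-year handling and denominators belong in a fuller document. That is fair for the details, and their absence is not the basis here. The basis is the measure the article chose: the same paragraph specifies adjusted incidence and prevalence and treatment proportions, but a plain number for events.

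Third, the same paragraph needs yearly numbers of incident and prevalent cases, so a reader could form a crude proportion if these are printed. That is partly right, and it would be too strong to say that nothing about risk can be recovered. Even so, a crude proportion would remain too low for a part-year 2019 and would ignore person-time and changes in age mix.

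Two stronger readings are tempting. A reader might infer that all the yearly results are distorted. The document does not support this: point prevalence and treatment proportions barely depend on how much of 2019 is observed, and AF incidence is too low only if part-year cases are divided by a full-year denominator, which is nowhere stated. A reader might also infer that the DOAC-versus-warfarin comparison is compromised. It is not: it rests on cause-specific and subdistribution hazard ratios and on cumulative incidence with censoring weights, which handle the end of follow-up by censoring. The article plans no test of the count trend and does not tie the yearly counts to a DOAC effect.

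**Conclusion.** The point holds for the descriptive yearly event series. On a calendar-year reading with 2019 shown, the 2019 counts cover at most about 41% of the year, a fall of at least about 59% at constant risk and constant number of cases. That size rests on the document's own dates, the calendar-year reading and an even spread of events. Before 2019, counts change with the number of AF cases at constant risk. How much cannot be taken from the document, which gives no yearly case numbers or network size; the factors of 1.20 to 2.00 illustrate assumed growth of 2% to 8% a year.

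The severity is minor to moderate. No primary estimate changes, but for TIAs and bleeds this series is all that the article offers against its aim on complications.

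**What to change.** - End the annual series on 31 December 2018. Alternatively, state the data cut and mark 2019 as a part-year with person-time counted to that cut.
- Report strokes, TIAs, deaths and bleeds as rates per 1,000 person-years with confidence intervals, beside the counts. Standardisation for age and sex is preferable, so that an ageing case mix does not pass for a change in risk.
- If AF incidence is shown for 2019, use person-time to the cut as its denominator too.

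The cost is some re-tabulation and possibly the loss of the last part-year. No new data collection should be needed if the registration dates held allow person-time to be computed. The Results section says that phase 1 analysis was complete by December 2019 and that publications were under review in October 2020. The change therefore means rerunning the yearly tables as well as rewording the plan.

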### Phase 2: Development of a Dashboard for Monitoring AF

We developed an online dashboard for the general practices to understand the quality of their data across a variety of AF-related indicators. The AF dashboard provided 4 categories of information: (1) case ascertainment—incidence, prevalence, standardized prevalence, and any indicators related to P4P prevalence; (2) indications for therapy and risk factors; (3) management choices; and (4) quality. The dashboard was developed using Tableau data visualization software (Salesforce Inc). The initial dashboard is hosted on the public dashboard cloud server and accesses a publicly accessible database server (located within information technology infrastructure of the University of Oxford), which hosts only aggregated data to comply with the requirements of information governance. The dashboard allowed users to view the AF indicators only from their own practice.

We used the Think Aloud method to validate the usability of the AF dashboard. During usability experiment, study participants were instructed to verbalize their thoughts while concurrently conducting predefined tasks on the dashboard [21]. The design of the Think Aloud experiment involved participants engaging in 5 tasks. Participants were asked to verbalize their thought process while engaging in each of the tasks [22]. During the initial 4 tasks, the participants interacted with the 4 main sections of the dashboard. They observed the given information and interpreted it with respect to that particular aspect of AF management in their practice. As a fifth task, participants considered the overall dashboard and described the overall state of AF management in their practice in comparison to the RCGP RSC sentinel network.

#### Participants

We invited staff from general practices to cover a range of roles from primary care, including general practitioners, nurses, and practice managers. We provided remote participation for those who could not attend in person. We aimed to invite staff from practices participating in the RCGP RSC sentinel network. Our target sample size was about 30 participants based on the guidelines from previous studies [23].

#### Data Capture and Analysis

We recorded participant feedback and screen activity using GoToMeeting screen sharing software, version 10.5 (LogMeIn Inc). The audio component of the recordings was exported and transcribed by a professional transcription service. The transcripts were analyzed using NVivo, version 12 (QSR International), a qualitative analysis software. We followed a 3-step approach to analyze the transcripts.

*Mapping verbalized tasks to sections:* Each verbalized task description was extracted and mapped to the corresponding section of the dashboard. A “verbalized task” is the narrative description provided by a participant when interacting with particular component in the dashboard. We organized the verbalized tasks according to the template given in (Table S1 in Multimedia Appendix 1). The verbalized tasks were mapped to the dashboard sections, and similar feedbacks were grouped.*Mapping verbalized tasks to usability problem classes:* For each section, we mapped the verbalized tasks to matching usability problem classes. We adapted the usability problem classification method used by Peute et al [21] and identified occurrences for each usability problem class (Table S2 in Multimedia Appendix 1). We also classified the identified verbalized tasks based on whether they were positive feedback, negative feedback, or suggestions for new features.*Summarizing usability issues across sections/usability problem class:* The completed templates were analyzed to determine the critical sections and key usability problem classes that required attention.

